### Sample size

The sample size calculations were carried using a target number of participants of 873 pupils from 35 schools with an average of 25 pupils per cluster (school) (range, 5 to 96 pupils), and a harmonic mean of approximately 17. The latter was used in sample size calculations (see below) to allow for variation in school sizes.

For the diarrhea intervention, the sample size is in terms of numbers of schools and numbers of children per school. For the dengue intervention, the sample size is in terms of numbers of schools, since the primary endpoint will be measured only in schools. In other words, cluster-randomization applies to the diarrhea endpoint, but, in practice, not to the dengue endpoint, since there is only one school per cluster.

#### Diarrhea intervention

The sample size for the primary endpoint of diarrhea incidence was calculated using methods for cluster-randomized trials [43]. Existing data from the study area were used to estimate baseline diarrhea incidence (0.28/person-year) and within-school clustering (coefficient of variation *k* = 0.8). For 17 children per school followed up for 2 years, 35 schools achieve 90% power for a 75% reduction in incidence and 5% two-sided significance level.

#### Dengue intervention

Baseline values of the primary dengue endpoint (*Ae. aegypti* adult density in schools) were based on values reported from Mexican schools [44], as no comparable data were available from Colombia. To allow for over-dispersion relative to Poisson, a negative binomial distribution was fitted to these data, yielding a mean of 24 mosquitoes per schools and dispersion parameter (*θ*) of 0.75. Then, power was estimated using the method of Brooker *et al.*[45] which assumes equal numbers per arm. Taking the above parameters and 17 schools per arm, a 70% reduction in numbers is detectable with 84% power, and 75% reduction with 92% power. The power is slightly higher for 18 *vs.* 17 schools, which are the numbers randomized per arm for each of the two main comparisons (Figure 2).

### Sequence generation and allocation concealment

Anapoima and La Mesa municipalities differ in ways which are likely to be associated with the trial outcomes. For example, La Mesa schools are located at higher altitudes (712 to 1,610 meters above sea level) than Anapoima schools (588 to 1,089meters above sea level). Furthermore, only Anapoima has a municipal educational board which potentially improves educational follow-up. We therefore decided to stratify based on municipality [46]. Allocation of schools to the different trial arms was carried out at an open-to-the-public randomization event in each municipality before the start of the school year. After fully informing the school principals and teachers of the purpose of the event a raffle was arranged where a representative of each school drew a number indicating to which arm of the trial their schools would be allocated. To minimize bias at the time of data analysis each school was assigned a unique code to blind the statistician analyzing the data. All schools were thus allocated publicly at the start of the trial, obviating the need for allocation concealment. Control schools will receive the interventions at the end of the project if these interventions effectively affect the outcome measures.

### Statistical methods

For the diarrhea outcome, clustering will be taken into account by analyzing the school-level rates. The above sample size method [43] assumes the analysis will be done by a *t*-test comparing such summary rates between two arms. This is equivalent to analysis of covariance (ANCOVA) with a single binary explanatory variable. For the current trial, additional explanatory variables are required to allow for: (a) two interventions rather than one; and (b) the stratification by municipality. The response variable (school-level diarrhea incidence) may be log-transformed if this results in a more normal (Gaussian) distribution of the residuals. A secondary analysis will include a further binary explanatory variable representing the interaction term between the two interventions.

The dengue outcome, *Aedes aegypti* density, will be summed over follow-up time points to give a single rate per school. This will be analyzed by negative binomial regression using the number of adults, and the logarithm of the sampling effort (that is, person-time spent aspirating) as an offset. Hence, this analysis will yield density ratios. As for diarrhea incidence, the explanatory variables for the primary analysis will be trial arm and stratum.

Neither of the above primary analyses will include an interaction term although these will be estimated in secondary analyses.

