**Methods/design:**

This is a 2×2 factorial cluster randomized controlled trial. Eligible schools were rural primary schools in La Mesa and Anapoima municipalities, Cundinamarca, Colombia. Eligible pupils were school children in grades 0 to 5. Schools were randomized to one of four study arms: diarrhea interventions (DIA); dengue interventions (DEN); combined diarrhea and dengue interventions (DIADEN); and control (C). Schools were allocated publicly in each municipality (strata) at the start of the trial, obviating the need for allocation concealment. The primary outcome for diarrhea is incidence rate of diarrhea in school children and for dengue it is density of adult female *Aedes aegypti* per school. Approximately 800 pupils from 34 schools were enrolled in the trial with eight schools in the DIA arm, nine in the DEN, eight in the DIADEN, and nine in the control arms. The trial status as of June 2012 was: completed baseline data collections; enrollment, randomization, and allocation of schools. The trial was funded by the Research Council of Norway and the Lazos de Calandaima Foundation.

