4. Knowledge, attitudes, and practices: Pre-designed questionnaires on the knowledge attitudes and practices will be administered to pupils and teachers.

5. Location: The geographical location of each school will be recorded by a handheld GPS and plotted in a GIS using available digitized base maps for spatial analyses and for presentation purposes.

6. Climate: General climate data (rainfall, temperature, and humidity) will be retrieved from hydrometereological stations of the Corporacion Autonoma Regional de Cundinamarca (CAR) for the Tequendama province, of which two are located in La Mesa municipality. At a local level, climate data will be collected in three selected schools in each municipality, based on differences in altitude and precipitation. Indoor maximum and minimum temperatures, indoor humidity, and rainfall will be measured twice daily (07:00 and 12:00) during school days. Data will be collected by school children with supervision of teachers.

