### Trial status

At the time of submission of this manuscript (June 2012) the trial had completed the baseline data collections, enrollment of schools, and randomized allocation of schools to the four study arms (Figure 2).

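### Between-school variation dominates this 34-school trial, yet neither primary model uses the school's baseline outcome; where it was measured, prespecifying it would improve precision (bias is not the issue)

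*Protocol article*

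**What the plan says.** In the Protocol article, Statistical methods, school-level diarrhea rates are analysed by ANCOVA, for which "additional explanatory variables are required to allow for: (a) two interventions rather than one; and (b) the stratification by municipality". The mosquito count is analysed by negative binomial regression with log aspirating time as offset, and "the explanatory variables for the primary analysis will be trial arm and stratum". The only extension named is the interaction between the two interventions, kept for secondary analyses.

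The Trial status section reports that by June 2012 "the trial had completed the baseline data collections, enrollment of schools, and randomized allocation of schools to the four study arms". Neither it nor the abstract lists what the baseline round measured. The outcomes table (Table 2) schedules adult mosquito collections at 4, 9 and 15 months after intervention, and Data collection methods gives the same times as the default.

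Stratification is justified in Sequence generation and allocation concealment because "Anapoima and La Mesa municipalities differ in ways which are likely to be associated with the trial outcomes". Altitude is the first example: "La Mesa schools are located at higher altitudes (712 to 1,610 meters above sea level) than Anapoima schools" (588 to 1,089 m). On size, the abstract says "Approximately 800 pupils from 34 schools were enrolled in the trial".

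**The concern.** The protocol assumes very large differences between schools: a coefficient of variation k = 0.8 for diarrhea and a dispersion parameter θ = 0.75 for mosquitoes. When most of the variance lies between schools, more pupils or more aspirating time per school help little. A school-level covariate that predicts the outcome can help. The obvious candidate is the same school's value before intervention, and the plan reports a completed baseline round but does not use it.

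Two things are at stake. One is power, which is already low for effects smaller than the 70% to 75% reductions targeted. The other is chance imbalance, since a raffle of about 34 schools into four arms can leave the arms different at the start, and a municipality term corrects only the part that lies between municipalities.

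**Working it through.** **Inputs** (Sample size section): diarrhea rate 0.28 per person-year, k = 0.8, 17 children for 2 years = 34 person-years per school, 75% reduction (0.28 to 0.07); mosquito mean 24, θ = 0.75, 17 schools per arm. Two-sided 5% is stated for diarrhea and assumed for mosquitoes.

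**1. Stated diarrhea figure.** Schools per arm = 1 + (1.96 + 1.282)² × [(λ0 + λ1)/y + k²(λ0² + λ1²)]/(λ0 − λ1)².
- Within-school term: 0.35/34 = 0.0103.
- Between-school term: 0.64 × (0.0784 + 0.0049) = 0.0533.
- Result: 1 + 10.51 × 0.0636/0.0441 = 16.2, so 17 per arm or 34 schools, against 35 stated. Power at 17 vs 17 is 91.5%, against 90% stated.

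**2. Stated mosquito figure.** Variance of the log density ratio = [(1/24 + 1/0.75) + (1/7.2 + 1/0.75)]/17 = 2.847/17 = 0.1675, so SE = 0.409. Power for a 70% reduction = Φ(1.204/0.409 − 1.96) = 83.7%, against 84% stated. For 75% it is 92.1%, against 92% stated. Both calculations reproduce without baseline adjustment.

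**3. Where the variance lies.**
- Diarrhea: 0.0533/(0.0533 + 0.0103) = 84% between schools.
- Mosquitoes: 2.667/2.847 = 94% overdispersion.

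**4. Chance imbalance.** With 17 vs 17 schools, the difference in a standardized covariate has SD √(2/17) = 0.34, so a gap above 0.5 SD has about a 14% chance per comparison. For gamma school effects with shape 0.75 the log-scale SD is 1.59. If the covariate's correlation with the log school effect is 0.5 (assumed), a 0.5 SD gap multiplies the expected density ratio by exp(0.5 × 0.5 × 1.59), about 1.5.

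**5. Ceiling on the gain.** Multiply the between-school component by (1 − r²), where r is the covariate's correlation with the true school-level outcome. The document gives no r, so a range is assumed.

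| r | 0 | 0.3 | 0.5 | 0.7 |
|---|---|---|---|---|
| Mosquitoes, 70% reduction | 84% | 87% | 92% | 98% |
| Diarrhea, 75% reduction | 91.5% | 93.4% | 96.3% | 99.1% |
| Diarrhea, 50% reduction | 53% | 57% | 63% | 76% |

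These are upper limits, because a real baseline value is measured with noise.

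**6. Simulated mosquito trials** (34 schools, mean 24, θ = 0.75, 70% reduction, test calibrated to a true 5%). The correlation is between baseline and follow-up school effects. Power without and with log baseline count, in separate sets of simulated trials:
- 0.3: 74% and 73%; 76% and 78%.
- 0.5: 78% and 80%; 74% and 81%.
- 0.7: 79% and 90%; 76% and 89%; 77% and 89%.

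The gain is thus −1 to 2 points, 2 to 7 points and 11 to 13 points. Power of the planned model should not depend on this correlation, so its spread of 74% to 79% is simulation noise, and the gains at 0.3 and 0.5 cannot be told apart precisely. Uncalibrated, the Wald test at 1.96 had a type I error of about 7% to 9% in the planned model and 7% to 11% with a covariate.

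**7. Diarrhea baseline noise.** A baseline of 3, 6 or 12 months expects 0.28 × 17 × 0.25, 0.5 or 1 = 1.2, 2.4 or 4.8 episodes per school. Reliability of the baseline rate is k²λ²/(k²λ² + λ/(17T)) = 0.43, 0.60 or 0.75. With an assumed six-month baseline, simulated variance fell 7% to 10% at correlation 0.5 and 14% to 19% at 0.7. At 0.7, power for a 50% reduction rose from 51% to 59%.

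**8. Cost in the ANCOVA.** Four parameters leave 30 degrees of freedom from 34 schools. One covariate moves the critical t from 2.042 to 2.045.

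**The case against.** The strongest reply is that nothing in the plan is wrong. The analyses respect the cluster, adjust for the stratifier and are unbiased under randomization, and the power statements agree with the models chosen. Adjusting for strata only is an accepted choice, and further adjusted analyses could sit in a fuller plan. Most of this stands. But the article states the primary covariate list outright, so the choice is made here and can be commented on.

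Four stronger readings are tempting, and the document supports none of them.
- **Bias or wrong power.** A reader might infer a biased analysis or a misstated power. Steps 1 and 2 rule out an arithmetic error. The lower simulated mosquito power in step 6 reflects the small-sample behavior of the Wald test, not the missing covariate.
- **Data already in hand.** The baseline content is not itemised, the listed collection times are all after intervention, and the Sample size section had to take mosquito density from Mexican schools. Its existing diarrhea data are not said to cover each trial school.
- **Altitude belongs in the primary model.** The ranges overlap between 712 and 1,089 m, and "The geographical location of each school will be recorded by a handheld GPS", so within-municipality variation exists. The document does not show that this variation predicts the outcome, and no gain from it was computed.
- **Adjustment is the only route to more power without more schools.** Nothing shows that.

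It is also fair that the benefit is conditional, and that adding a covariate slightly worsens the Wald test's size unless a small-sample reference is used.

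**Conclusion.** The point holds as an efficiency recommendation. Both primary models leave out the covariate most likely to explain the variation that limits this trial. For mosquitoes the gain is small at a correlation of 0.3 to 0.5 and about 12 power points at 0.7. For diarrhea it is probably modest unless the baseline period is long. Apart from simulation noise, adjustment did not cost mosquito power in the scenarios examined.

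This rests on three assumptions: that the completed baseline round measured the outcome in each school, that the correlation lies in the range shown, and that the protocol's k and θ apply to these schools. If the first fails for an outcome, there is nothing to change for that outcome's covariates.

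**What to change.** First state what the baseline round measured in each school. Then, before any outcome analysis:

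1. **Mosquitoes.** Where measured, add log(baseline adult *Aedes* count + 1) to the primary negative binomial model, allowing for baseline sampling effort.
2. **Diarrhea.** Where measured, add the school's baseline diarrhea rate to the primary ANCOVA.
3. **Sensitivity.** Keep the arm-plus-stratum models as sensitivity analyses. Altitude is at most an optional sensitivity covariate for mosquitoes.
4. **Reference distribution.** Judge the negative binomial model against a small-sample reference, for example a t or permutation test, instead of 1.96. This is needed with or without the covariate.

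The cost is one degree of freedom per model and a slightly greater need for item 4. If the baseline values exist the change is one of wording; if they do not, items 1 and 2 fall away.

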### Data collection methods

Both quantitative and qualitative methods will be employed to address the objectives of this research. Data will be collected at 4, 9, and 15 months post-intervention, unless otherwise mentioned. The project will involve the following methods:

1. Health: Pupils’ absences from school for health reasons will be recorded and confirmed by phone calls to parents and, if necessary, house visits made by a health technician and supervised by the project physician. Probable dengue cases will be defined according to WHO criteria [13]. Data for pupil absences will be recorded daily by teachers and collected weekly by project staff.

2. Entomology: Dengue vector infestation and abundance will be evaluated by adult and immature collections. Adult mosquito collections will be carried out inside schools with a battery-driven Prokopack aspirator [47] for 10 to 15 min in each classroom. Immature collections will be carried out in containers in schools. The immature collection enables the calculation of various immature indices, of which the Breteau index (number of positive containers/100 schools) and the number of pupae in relation to human population (number of *Ae. aegypti* pupae/person) are the most important. *Aedes* pupal productivity survey methodology allows for identification of the most epidemiologically important container types [48]. Water-holding containers in schools and their peri-domestic environments will be identified, counted, measured, and classified according to shape (S), use (U), and material (M) using the standardized container classification methodology (SUM-method) [49]. Mosquitoes will be identified in the field laboratory using common identification keys (for example, [50,51]).

3. Water quality: Fecal contamination and physicochemical parameters of stored water in schools. Presence of *E. coli* will be used as a proxy for risk of diarrheal infections according to WHO guidelines [6]. In each selected school, samples from all drinking water containers and taps will be collected for both *in situ* tests (temperature, pH, electrical conductivity, and total dissolved solids) and laboratory analysis (fecal coliforms and *E. coli*) following standard methods [52]. Each sample bottle will be labeled with school and container codes and transported on ice to a certified laboratory (Daphnia Laboratory, Bogotá, Colombia) for analysis.

4. Knowledge, attitudes, and practices: Pre-designed questionnaires on the knowledge attitudes and practices will be administered to pupils and teachers.

5. Location: The geographical location of each school will be recorded by a handheld GPS and plotted in a GIS using available digitized base maps for spatial analyses and for presentation purposes.

6. Climate: General climate data (rainfall, temperature, and humidity) will be retrieved from hydrometereological stations of the Corporacion Autonoma Regional de Cundinamarca (CAR) for the Tequendama province, of which two are located in La Mesa municipality. At a local level, climate data will be collected in three selected schools in each municipality, based on differences in altitude and precipitation. Indoor maximum and minimum temperatures, indoor humidity, and rainfall will be measured twice daily (07:00 and 12:00) during school days. Data will be collected by school children with supervision of teachers.

### Publication policy

The principal investigators will ensure that the results of this trial are published regardless of outcomes. Reporting of the trial results will follow the guidelines of the CONSORT statement [32].

### Ethical review

The study will be conducted according to the Declaration of Helsinki and the International Guidelines for Ethical Review of Epidemiological Studies. This trial was approved by the Comité Institucional de Ética en Investigaciones de la Universidad El Bosque, Bogotá, Colombia on 30 August 2011 (Acta No. 146). The trial protocol was reviewed by the Regional Committees for Medical and Health Research Ethics (REC) in Norway.

## Discussion

To our knowledge this is the first trial investigating the effect of a set of interventions to control both diarrheal diseases and dengue fever. This is also the first trial to study the combination of diarrhea-dengue disease control in school settings. Diarrheal diseases originating from contaminated drinking water due to poor water collection and storage practices may be epidemiologically linked to dengue fever, whose mosquito vectors breed in stored water containers. Thus, containers used to store water may be the link between the two diseases. By integrating disease interventions it may be possible to effectively and cost-efficiently control disease outcomes. A 2×2 factorial design is a logical choice for evaluating two related sets of interventions.

The study area is fairly suitable for the current study as both diseases are prevalent in the two selected municipalities. We are also familiar with the study area from previous studies conducted there. It was decided to set the trial in small rural primary schools for several reasons: rural areas are often neglected in terms of national health policies which is reflected in reports on global rural–urban disparities for access to safe water and improved sanitation [4]; dengue control primarily takes place in urban areas, although dengue transmission is also a problem in rural areas [12,36]; small rural schools are logistically feasible and fairly uncomplicated to manage (although sometimes difficult to access during the rainy season). In Colombia between 13% and 29% of dengue cases are reported from rural areas [53-55], with the highest number from the present study area [55]. Finally, only relatively few studies have investigated the effect of health interventions in schools in developing countries (for example, [56,57]). Further, school children may act as mediators of health messages to their parents and the community [58]. With the interventions being implemented at the school level, it follows that the school should also be the unit of randomization, resulting in a cluster-randomized design. Our primary diarrhea endpoint is disease, but this is not the case for dengue. For diarrhea, parents are best placed to evaluate the WHO definition of diarrhea in terms of stool frequency and consistency, while dengue cases are difficult and expensive to confirm by laboratory tests and statistical power is problematic due to large between-year variation in incidence. Hence we have chosen a dengue vector endpoint, specifically the density of adult *Aedes* mosquitoes, this being more proximally related to disease than the *Stegomyia* indices used in some previous trials.

It should be noted that the current study design evaluates two sets of interventions and so, within each set, the effects of single interventions on the outcome measures cannot be distinguished. It is the overall effect of each of these two sets of disease-specific interventions that is of interest in this study.

### Trial status

At the time of submission of this manuscript (June 2012) the trial had completed the baseline data collections, enrollment of schools, and randomized allocation of schools to the four study arms (Figure 2).
